### Objectives and hypotheses

In order to advance CBT- and mindfulness-based intervention research for employees, the objectives of the present randomized control trial are: a) to evaluate the effectiveness of a MBSR intervention on psychological detachment and well-being indicators; b) to evaluate the effectiveness of a CBT-based intervention on psychological detachment and well-being indicators; c) to compare the strength of the effects of both protocols; d) to determine which mechanisms are responsible for the intervention effects (i.e., mediators) and test whether these mechanisms are general or intervention-specific; e) to explore boundary conditions (i.e., moderators) which attenuate or accentuate intervention effects. To determine the decisive ingredient in CBT-based and mindfulness interventions, the CBT protocol will predominantly be aimed at identifying and changing maladaptive thinking patterns and associated behaviors. The MBSR protocol, on the other hand, will predominantly include exercises that focus explicitly on increasing present moment awareness by using established exercises that aim to improve mindfulness practices [14, 38]. Although research has found that both CBT and MBSR protocols are effective with respect to employee well-being [14, 17, 18, 24], we tentatively assume that the CBT protocol will be superior for most of the studied outcomes as it is theory-driven, well-researched, and empirically supported for a wide range of conditions including moderate to severe symptoms of several psychological disorders [39]. It may also be more appropriate for targeting an important underlying factor contributing to poor detachment and burnout (i.e., maladaptive thinking patterns) [40]. Moreover, interventions that include some form of CBT exercises along with other exercises are found to be most effective [17, 18, 22, 41]. More precisely, we hypothesize that the CBT-based intervention will lead to higher levels of psychological detachment from work directly after the intervention (T2) and at follow-up (T3) compared to levels prior to the intervention (T1) and to MBSR and control groups. Additionally, we assume that the CBT-based intervention will lead to enhanced (general and work-specific) well-being directly after the intervention (T2) and at follow-up (T3) compared to levels prior to the intervention (T1) and to MBSR and control groups. In line with previous studies (e.g., [41]), a wider range of general (life satisfaction, depression, anxiety, stress, positive and negative affect, sleep quality) and work-related well-being (work engagement, workaholism, work-family conflict) outcomes will be assessed. Along with psychological detachment from work, burnout also represents a primary outcome as both interventions will be adapted to the work context and conditions of high job demands.

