## Methods/design

### Study design

The randomized controlled trial will follow the recommendations of the CONSORT (Consolidated Standards of Reporting Trials) group, which is considered a gold standard in clinical practice regarding devising interventions as well as their reporting [43]. The study design is depicted in Fig. 1. The study will take place between October 2020 and February 2021. In order to reach the target sample size, the second round of data collection will take place between January 2021 and May 2021, and additional rounds of data collection will be carried out if needed. Data collection in both intervention groups (i.e., CBT- and MBSR protocol) and the control group will be carried out immediately before (T1) and after the intervention (T2). During the 6-week intervention period, weekly questionnaires will be sent out to participants. The follow-up data collection will take place 3 months after the end of the intervention (T3). During T1, T2 and T3, participants will be asked to fill out questionnaires addressing all studied constructs, whereas the weekly questionnaire will only encompass the central mechanisms and primary study outcomes (i.e., work-related maladaptive thinking patterns, mindfulness, psychological detachment, and burnout). During the intervention period, participants from both intervention groups will receive e-mail notifications every Monday and Thursday with information about the assignments and exercises. The initial e-mail will include instructions on how to access the online platform with CBT and MBSR exercises. The notification every Monday will remind participants to fill out the weekly questionnaire before they start with the new exercise. All exercises from previous weeks will be visible on the online platform. Upcoming exercises will not yet be available to ensure that participants will not skip the activities or perform them in random order. The online platform will automatically monitor whether the participants followed the instructions and performed the respective exercises. In case of non-compliance, reminders will be sent out the following day. After the intervention, participants from the waitlist control groups will receive access to the online platform and all intervention materials, which they can perform in any order. They will receive weekly e-mails reminding them to perform the exercises and encouraging them to practice them. After the intervention, each participant will have the opportunity to request individualized feedback on his or her results.

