
Notwithstanding these limitations, the proposed intervention study is one of the first that is explicitly directed at comparisons between two protocols and mechanisms of change. Both notions are important, as the results may inform theory about psychological detachment and lead to the identification of decisive intervention ingredients. With the focus on work-related maladaptive thinking patterns [40, 84], the work-related well-being literature will potentially gain understanding of a new yet poorly understood, personal vulnerability factor that makes employees more susceptible to ill-being at work or even psychological disorders. Another strength of the intervention is the control of relevant confounding factors. Although the online intervention design may have some drawbacks, the contamination of experimental and control groups will not be a cause for concerns. As participants will not be recruited from one or a small number of organizations and will individually apply for the study, exchanges between participants from different intervention groups are not likely. Given the online protocol, intervention effects also cannot be attributed to positive and supportive interactions between participants [14]. As participants will be blinded to the intervention, the possibility of attenuated or accentuated intervention effects due to participants’ expectations will be minimal. Finally, both online interventions can be utilized by a wide range of professions and can easily be adapted to different workplace contexts and work schedules. The weekly monitoring of effects will further help to customize and shorten similar interventions in the future. As such, the protocol has the potential to significantly advance knowledge about evidence-based CBT and mindfulness interventions and holds promise to be highly applicable to organizational settings.

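### Read plainly, the waitlist arm receives both programmes before the 3-month follow-up, so the T3 contrasts with control are diluted to an unknown degree

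*Protocol article*

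**What the plan says.** Four statements in the protocol article bear on this.

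- **Assessment times (Study design).** Data collection is "carried out immediately before (T1) and after the intervention (T2"), with follow-up (T3) three months after the intervention ends.
- **Waitlist access (Study design).** "After the intervention, participants from the waitlist control groups will receive access to the online platform and all intervention materials", to be used in any order. The next sentence adds: "They will receive weekly e-mails reminding them to perform the exercises and encouraging them to practice them". The platform is described as holding both sets of exercises: "The initial e-mail will include instructions on how to access the online platform with CBT and MBSR exercises".
- **Hypotheses (Objectives and hypotheses).** CBT is expected to give better psychological detachment, and in a parallel sentence better well-being, "directly after the intervention (T2) and at follow-up (T3) compared to levels prior to the intervention (T1) and to MBSR and control groups".
- **Analysis (Effect evaluation).** Each primary outcome gets a time (pre, post, follow-up) by group (CBT, MBSR, control) repeated-measures ANOVA. Significant interactions are followed by simple effects with Bonferroni correction.

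Participants and recruitment adds only that the waitlist arm will be told of a delayed start to its training. It gives no date and makes no link to T3.

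**The concern.** The sentence that opens access for the waitlist arm uses the same wording that places T2, and T3 has its own label. Nothing in the text shown holds access back until T3 has been collected. If the plan is followed as written, the group called control at follow-up has had the CBT and MBSR materials, with weekly prompting, for some or all of the preceding three months. The programme lasts six weeks (Intervention design), so it fits inside that interval.

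The T3 contrast with control then compares immediate with delayed access. Whatever benefit the waitlist arm draws from the materials is subtracted from the observed difference. A small or null T3 difference could mean that the CBT effect wore off, that the waitlist arm caught up, or both. Durability against control is part of a primary-outcome hypothesis, so this affects what the trial can conclude. The Strengths and limitations section does not mention it.

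**Working it through.** **1. The plan's own sample size.** For the group-by-time interaction (3 groups, 3 times) with f(V) = .25 and α = .05: df1 = 2 × 2 = 4, df2 = 2(N − 3), λ = 2 × N × 0.25².

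- N = 151: df2 = 296, λ = 2 × 151 × 0.0625 = 18.875, power .950.
- N = 98: df2 = 190, λ = 12.25, power .800.

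Both stated figures reproduce, so the sample-size arithmetic is not at fault.

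**2. Dilution at T3.** Inputs from the protocol: about 50 per group (N = 151) or 33 per group (N = 98), and α = .05. Assumptions not in the protocol: a sustained true difference from untreated control of d = 0.5, and a fraction u of that benefit gained by the waitlist arm before T3.

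Observed difference: 0.5 × (1 − u). Two-sample t-test with n per group: noncentrality = 0.5(1 − u) × √(n/2), df = 2n − 2. For n = 50, √(50/2) = 5; for n = 33, √(33/2) = 4.062.

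| u | Observed d | Noncentrality, n = 50 | Power, n = 50 | Noncentrality, n = 33 | Power, n = 33 |
|---|---|---|---|---|---|
| 0 | 0.500 | 2.500 | .70 | 2.031 | .52 |
| .25 | 0.375 | 1.875 | .46 | 1.523 | .32 |
| .50 | 0.250 | 1.250 | .24 | 1.016 | .17 |
| .75 | 0.125 | 0.625 | .09 | 0.508 | .08 |

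These use unadjusted two-sided .05. The plan names Bonferroni for the follow-up tests. Taking three group pairs (an assumption, α = .05/3 = .0167), the same formula gives .53, .29, .12 and .04 with 50 per group, and .34, .18, .08 and .03 with 33.

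**3. The omnibus interaction.** Assume both active arms sit at d = 0.5 at T2 and T3, and the waitlist arm is at 0 at T2 and 0.5u at T3. With unit SD and within-person correlation ρ, λ = (N/3) × S/(1 − ρ), where S is the sum of squared interaction residuals of the nine cell means. S is 0.1111 at u = 0, 0.0833 at u = .5 and 0.1111 at u = 1.

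- N = 151, ρ = .5: λ = 50.33 × 0.1111/0.5 = 11.19, power .76 at u = 0; λ = 8.39, power .62 at u = .5; power .76 again at u = 1.
- N = 151, ρ = .7: .95, .86 and .95.
- N = 98, ρ = .5: .55, .42 and .55.

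The omnibus test therefore keeps much of its power, because the T2 separation carries it. It is as strong when the waitlist arm has caught up completely as when it has gained nothing, so a significant interaction does not by itself show a lasting difference.

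**4. What is untouched.** T2 contrasts with control precede the access. CBT versus MBSR at T3 does not involve the waitlist arm. Change from T1 within the CBT arm is not altered by what the waitlist arm receives.

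**The case against.** Several points on the other side are sound.

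- **The access date is a reading.** No date is stated, Fig. 1 is not shown, and the delayed start is undated. Access could in practice follow T3. If so, the Study design wording still needs to say so. What stands is that, read plainly, access precedes T3 and nothing shown says otherwise.
- **A reader might infer that the T3 hypothesis cannot be tested at all.** That goes too far. Immediate versus delayed access is still a randomised comparison. If the materials help the waitlist arm or do nothing, the bias is toward no difference, so a clear T3 advantage for CBT would be conservative evidence of a lasting effect.
- **A reader might infer that the results will necessarily look like fading.** The planned analysis gives means by arm and time. Level active arms with a rising waitlist arm would look different from falling active arms. The cause of a late rise in the waitlist arm would remain uncertain.
- **A reader might see a contradiction with the statement that "the contamination of experimental and control groups will not be a cause for concerns".** There is none. The sentence after it in Strengths and limitations shows that it concerns exchanges between participants in different arms, not access that the trial itself provides.
- **Uptake may be low.** Use is voluntary and in any order, so dilution may be slight. Its size cannot be known from the document.

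These points narrow the concern but do not remove it: the T3 contrast with control, as labelled and hypothesised, is diluted by an unknown amount.

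**Conclusion.** The point holds in a limited form. Following the plan as written, T3 differences from control are biased toward zero in proportion to the benefit the waitlist arm draws from the materials, and a null or shrinking T3 difference cannot be attributed to loss of effect. Under the assumed d of 0.5, a waitlist gain of half the benefit cuts pairwise power from .70 to .24 with 50 per group and from .52 to .17 with 33, and further under Bonferroni. These figures rest on an assumed effect and assumed gains; they show a range and do not predict a result. The conclusion also rests on the plain reading that access begins before T3. The damage is confined to the T3 contrasts with control and how they are interpreted.

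**What to change.** Reconcile the access timing in Study design with the T3 hypothesis in Objectives and hypotheses by stating when waitlist access starts relative to T3.

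If access precedes T3:

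- make T2 the time point for CBT-versus-control and MBSR-versus-control claims;
- use T3 for the randomised CBT-versus-MBSR comparison;
- describe any T3 contrast with the waitlist arm as immediate versus delayed access, conservative for a lasting effect, and do not read a null result as loss of effect;
- report waitlist use of the platform beside that contrast, if it is logged. The article describes monitoring against the instructed schedule and does not say that any-order waitlist use is recorded.

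The cost is rewording of the hypotheses and of the Effect evaluation section, with no new assessments. The trial gives up a claim of superiority over an untreated control at three months, which a waitlist arm with earlier access cannot support.

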#### Background variables

In the pre-screening questionnaire, participants will be asked to provide some basic demographic data (i.e., gender, age, the highest level of formal education and family status), basic information regarding their work (i.e., employment status, type of work, weekly working hours, tenure, leadership status and whether they are currently on sick leave) as well as some intervention-related data (i.e., willingness to dedicate enough time to the intervention, access to the internet, self-rated competency to use a computer, involvement in other forms of psychotherapy/psychoeducation, prescription of drugs to treat mental illnesses and the presence of a mental illness diagnosis).

In the questionnaire that will be administered at T2 (directly after the intervention), they will additionally be asked to report any significant work- (e.g., switching jobs), private life- (e.g., switching apartments), or intervention-related (e.g., participating in other interventions, aimed at improving mental health) changes during the last 6 weeks. They will also be asked to rate their overall satisfaction with the intervention, their attitudes towards the exercises, their previous experience with similar exercises, and their self-reported adherence to the intervention procedure.

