### Statistical analysis

#### Sample size calculation

The G*Power 3.1 software was used to determine the minimum number of participants that need to be recruited [64]. We set the expected effect size to medium (*f(V)* = .25), the probability of a Type I error to α = .05, the statistical power (1-β) to .95 and chose a two-way repeated measures MANOVA (multivariate analysis of variance) with time (3 levels: pre, post, and follow-up) as the within-subjects factor and group (3 levels: CBT, MBSR, and control) as the between-subjects factor as the main statistical test. Given these specifications, the required total sample size is 151 participants (approximately 50 participants per group). In case of non-adherence and/or drop-out, the total sample size of 98 participants (approximately 33 participants per group) suffice with a more standard power level of .80.

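### Individualized feedback can be requested before the 3-month follow-up, so it can affect self-reported T3 outcomes; holding it until after T3 is a cheap improvement

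*Protocol article*

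**What the plan says.** The Study design section of the protocol article closes its account of procedures with this offer: "After the intervention, each participant will have the opportunity to request individualized feedback on his or her results". It is made to everyone in all three arms and is taken up on request. The article does not describe the content of the feedback or give a delivery date relative to T3.

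The same section places T1 and T2 immediately before and after the programme and then sets the last assessment: "The follow-up data collection will take place 3 months after the end of the intervention (T3"). Shortly before the feedback sentence, the same opening phrase marks the start of waitlist access: "After the intervention, participants from the waitlist control groups will receive access to the online platform and all intervention materials".

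Under Objectives and hypotheses, CBT is expected to do better on detachment and well-being "directly after the intervention (T2) and at follow-up (T3) compared to levels prior to the intervention (T1) and to MBSR and control groups". T3 therefore carries a within-arm claim (against T1) and a between-arm claim (against MBSR and control).

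Under Background variables, the T2 questionnaire asks about work, private-life and intervention-related "changes during the last 6 weeks", which covers the programme period. The article describes no matching question for the interval from T2 to T3.

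**The concern.** The primary and secondary outcomes are all self-report questionnaires, and T3 repeats scales the participant has already completed. Someone who has been told about their own results may answer the next round with those results in mind, or may act on them. Either could move a T3 score for reasons other than the durability of the programme.

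Two features make this more than noise. Uptake is self-selected after randomization, so it may depend on arm and on how the participant fared at T2. And the feedback concerns the participant's own results: if the programmes differ as hypothesized, what people are told will differ by arm even when equal numbers ask.

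At stake are the T1 to T3 change within each arm and the T3 contrasts, above all CBT versus MBSR. The article also relies on blinding participants to keep expectation effects small (Participants and recruitment; Strengths and limitations), and feedback on results before the last assessment works against that aim.

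This point is separate from waitlist access to the materials, which affects the T3 control contrasts and leaves CBT versus MBSR alone.

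**Working it through.** **Step 1: what the time reference means.** Objectives and hypotheses, Measures and Background variables all gloss T2 as directly after the intervention, and Study design dates it immediately after. T3 is called the follow-up, or is dated 3 months from the programme's end. On that usage the feedback offer opens at about T2. The phrase could also cover the time after T3, but nothing in the article closes the interval between T2 and T3. Feedback before T3 is permitted; it is not scheduled.

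**Step 2: whether any planned figure changes.** Inputs from Sample size calculation: f(V) = 0.25, alpha = 0.05, 3 groups, 3 times, power 0.95 (fallback 0.80). For the group-by-time interaction with Pillai's trace, s = 2, df1 = 4, df2 = 2(N − 3) and noncentrality = N × 2 × 0.25².
- N = 151: df2 = 296, noncentrality 18.875, power 0.9500.
- N = 98: df2 = 190, noncentrality 12.25, power 0.8005.

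Both stated sample sizes reproduce. Feedback timing enters none of these inputs, so there is no corrected figure.

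**Step 3: how feedback would enter the T3 estimates.** Let u be the proportion of an arm that receives feedback before T3, and d the mean shift it causes in those recipients, in SD units.
- Shift in one arm's T1 to T3 change = u × d.
- Bias in the T3 contrast of arms A and B = uA × dA − uB × dB.

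If u and d are the same in every arm, the between-arm expression is zero. The common shift then goes into the time effect and leaves the planned group-by-time interaction alone, but it still alters each arm's change from T1.

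**Step 4: illustration on assumed values.** The documents give neither u nor d, so these ranges are assumptions without an anchor in the article.
- Within one arm, u from 20% to 60% and d from 0.1 to 0.3 SD: from 0.2 × 0.1 = 0.02 SD to 0.6 × 0.3 = 0.18 SD.
- Between arms, same d, equal uptake: 0.
- Between arms, same d, uptake gap of 10 to 50 points: from 0.1 × 0.1 = 0.01 SD to 0.5 × 0.3 = 0.15 SD.
- Between arms, equal uptake of 20% to 60%, effects differing by 0.1 to 0.2 SD because the content differs: from 0.2 × 0.1 = 0.02 SD to 0.6 × 0.2 = 0.12 SD.

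The direction is not known either. Feedback could widen or narrow a difference.

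**The case against.** The strongest reply is that the offer is identical in all arms. An equal offer does not by itself bias a randomized contrast; that needs a difference in uptake, content or effect, and the documents report none. This stands. It is why no between-arm bias can be asserted, and why the 0.18 SD figure, which is a shift in one arm's mean, must not be read as bias in CBT versus MBSR. It does not dispose of the within-arm comparison with T1, where equal uptake does not cancel.

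A reader might infer more than the text supports in four ways:
- **That feedback is delivered before T3.** The sentence gives an opening point and no delivery date, and results could include those from T3.
- **That feedback goes unrecorded.** The article is silent on logging, a detail that a condensed article commonly leaves to the full protocol. Silence is no finding here.
- **That feedback is a co-intervention.** The article describes no advice, norms or therapeutic content.
- **That the data could never separate feedback from programme durability.** Recipients have to ask, so they are identifiable in principle, and the T2 contrasts and weekly growth curves precede the offer.

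It is also fair to say that waitlist access to all materials is the larger threat to the T3 control contrasts. That lends no weight to this point, nor does it answer it for the two active arms.

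**Conclusion.** The point holds in limited form. On the article's own usage, the feedback offer can fall between T2 and T3, ahead of self-reported outcomes that carry stated hypotheses. It could shift T1 to T3 change within an arm. It could bias T3 contrasts between arms, CBT versus MBSR included, if uptake, content or effect differs by arm.

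The size is unknown. It is zero between arms with equal uptake and effect, and every non-zero figure above rests on assumed values. The documents do not support a conclusion that the T3 comparisons are biased. The sample size and the T2 comparisons are not affected. This is an inexpensive improvement to the design, and its force comes from timing: feedback given before T3 cannot be withdrawn afterwards.

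**What to change.** Reword the closing sentence of Study design so that individualized feedback may be requested only after the participant's own T3 measurement, and align the participant information. The cost is one sentence and a wait of about 3 months for those who want feedback.

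If any feedback is released sooner, record its date and the participant's arm, and report uptake by arm alongside the T3 results. Do not exclude recipients from the main T3 comparison: receipt is a choice made after randomization, and dropping people on that basis would break the randomized comparison and could add selection bias of its own.
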